### Ethical approval

This trial (protocol number NL42210.018.13) is being performed in accordance with the Declaration of Helsinki [66] and received ethical approval by the Institutional Review Board “Medisch Ethische Toetsingscommissie Academisch Medisch Centrum” (Medical Ethics Committee of the Academic Medical Center in Amsterdam, the Netherlands) on July 24, 2014. The present study protocol, version 5 (April 1, 2015), has received ethical approval by the latter Institutional Review Board on April 20, 2015. Plans for important protocol modifications will be communicated to the Institutional Review Board, ClinicalTrials.gov and the Netherlands National Trial Register.

### Safety monitoring

In order to (1) protect the rights and well-being of human subjects; (2) ensure that trial data are accurate, complete and verifiable from source documents; and (3) ascertain that the conduct of this trial is in compliance with the currently approved protocol, with Good Clinical Practice (GCP), and with applicable regulatory requirements, this clinical trial is being monitored by a GCP-trained, independent monitor, who is not involved in the clinical trial as part of the trial staff. The monitor will report findings before, during and after the trial.

### Harms

Every adverse event related to the study intervention will be reported on the case report form by the dental surgeon. Participants are insured for harm during and within four years after the end of the trial.

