**Discussion:**

This randomized trial is the first to test the efficacy of 120 mg of perioperative propranolol versus placebo in reducing short-term (“state”) anxiety during dental extraction, fear memory reconsolidation, and lasting dental (“trait”) anxiety in a clinical population. If the results show a reduction in anxiety, this would offer support for routinely prescribing propranolol in patients who are fearful of undergoing dental extractions.

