#### First postoperative assessment

At completion of the surgical procedure, the dental surgeon will fill out the CRF containing the operative variables. Before leaving the clinic, the patient will again be shortly interviewed by the investigator. Only after the first dental extraction procedure will another semi-structured interview be conducted. This is meant to construct an approximately 30-second personal memory script portraying this first dental extraction procedure that the participant has just experienced (M2). The participant will subsequently receive one final capsule containing 40 mg of propranolol or placebo. The participant will be asked to fill in a small “intrusions diary” at home.

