#### Second dental extraction procedure

At the 1-month follow-up, a second dental extraction at the hospital will be performed, this time without the study medication. Administration of all questionnaires before and after the procedure will be repeated, but this time, no full-intrusions interview will be conducted. During the second procedure, a regularly used local anesthetic solution of articaine 4 % with adrenaline (1:200,000) will be administered. At completion, the surgeon will fill out another CRF, and the participant will be asked to keep another “intrusions diary”.

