The weeks after the dental extractions, the frequency and nature of intrusive thoughts will be indexed using an intrusions diary. Study participants will be asked to record their frequency and nature of their thoughts of the crucial traumatic event that exacerbated or initiated their dental anxiety (M1) for 7 days following the first and second dental extraction procedure.

A number of specific memory characteristics regarding the event that exacerbated or initiated their dental anxiety (M1) will be assessed using a 16-item self-report *Memory Characteristics Questionnaire (MCQ),* on two subscales; re-experiencing (eight items), disorganization (six items), peritraumatic dissociation (one item) and depersonalization and/or derealization during memory retrieval (one item) [65]. All 16 items are rated on a four-point scale ranging from “never” (0) to “all the time” (3).

The patients’ experiences during surgery will be assessed using visual analog scales (ranging from 0 to 100). Directly after the first and second (follow-up) dental extraction procedure, characteristics of participants’ experiences during surgery will be determined. Patients will be asked to rate the propensity of pain experienced during treatment, the degree of experienced reassurance/comforting by their surgeon, the sense of “here and now” when thinking back at this experience and how pleasurable the experience was. Patients will be asked to rate these characteristics on standardized continuous self-report VASs ranging from 0 (for example, “not reassured at all”) to 100 (for example, “completely reassured”).

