#### Operative variables

A number of operative variables will be recorded by the surgeon after the first and second dental extraction procedure. These include the nature of the procedure (extraction/surgical removal; numbering of the dental elements extracted using the FDI World Dental Federation/ISO 3950:2009 notation), duration of the surgery, difficulty (that is, whether the surgery was experienced as a “complicated procedure”), number and location of anesthetic capsules administered, observer-rated anxiety (surgeons are asked to rate the question “according to you, how much anxiety did the patient show during treatment” using a continuous observer-rated VAS ranging from (0) “no anxiety at all” to (100) “extremely anxious”), nature of the follow-up treatment, and information on the occurrence of any adverse events.

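### The article gives two different scopes for adverse-event recording, and describes no adverse-event contact between the final capsule and the second extraction

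*Protocol article*

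**What the plan says.** The Harms section states: "Every adverse event related to the study intervention will be reported on the case report form by the dental surgeon". It gives no time window and does not say who decides whether an event is related.

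The Operative variables section lists, among the surgeon's items, "information on the occurrence of any adverse events". On when these items are collected it says: "A number of operative variables will be recorded by the surgeon after the first and second dental extraction procedure".

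The First postoperative assessment section gives the order at the treatment visit. First: "At completion of the surgical procedure, the dental surgeon will fill out the CRF containing the operative variables". The investigator then briefly interviews the patient and builds the script of the extraction just experienced. Then: "The participant will subsequently receive one final capsule containing 40 mg of propranolol or placebo".

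For the time at home the article describes an intrusions diary: "Study participants will be asked to record their frequency and nature of their thoughts of the crucial traumatic event". The message sent the day after treatment is a reminder to complete that diary. At the second visit, where no study medication is given: "At completion, the surgeon will fill out another CRF".

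**The concern.** Two things are at stake.

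- **Scope.** The placebo arm allows event rates to be compared without deciding, event by event, what the drug caused. If relatedness is a condition for entering an event at all, that comparison loses events before the arms are set side by side. If every event is entered, it does not. The article states both rules, so two surgeons at two sites could each follow a printed sentence and keep different records.
- **Timing.** The last capsule is meant to act in the hours after surgery. If the first-visit form is already complete by then, events in those hours depend on some later contact to be picked up.

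The abstract raises the importance of both. It says that if anxiety is reduced, "this would offer support for routinely prescribing propranolol". The Background and Discussion present safety as part of the case for a new intervention. A reader will therefore look to this trial for safety information, and 34 participants will supply few events.

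**Working it through.** The plan gives no figure on this point to reproduce. The check compares sections and adds some short arithmetic.

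**1. Scope.** Both rules concern what the surgeon enters on a case report form, since the First postoperative assessment section says the surgeon's form holds the operative variables. Take an event the recorder thinks unrelated to the capsules:
- under Harms, its entry is not required;
- under Operative variables, it is entered.

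The same event gives two different records.

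**2. Order and share of dose.** The dose is 2 × 40 mg before surgery and 1 × 40 mg after, 120 mg in total. The text places the surgeon's form first, the interview second and the last capsule third. Share of dose after the form: 40 / 120 = 33%. This is a share of dose, not of missed events.

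**3. Exposure after the form.** The Active substance section gives a half-life of about 4 hours. Under simple exponential decay, ignoring absorption, the last 40 mg leaves:
- at 4 hours: 40 × 0.5^(4/4) = 20 mg;
- at 8 hours: 40 × 0.5^(8/4) = 10 mg.

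Exposure continues for hours after the form. The same section says this is the purpose of the last capsule. No discharge time is given, so the part falling at home cannot be computed.

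**4. Described contacts after the last capsule.**
- Blinding question, asked once all medication has been taken: treatment guess only.
- Next-day message: diary reminder.
- Seven-day diary: thoughts about the crucial fear-related memory.
- Preoperative interview at the second visit: no adverse-event item in Tables 1 or 2.
- Surgeon's form after the second extraction, about 4 weeks later: includes adverse events, with no stated look-back period.

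Only the last is described as collecting adverse events, and it is completed just after a new procedure.

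**5. How much a small record can show.** With 1:1 allocation, 34 / 2 = 17 per arm. If no event of some kind occurred in 17 treated patients, the one-sided 95% upper limit for its rate would be 1 − 0.05^(1/17) = 16.2%. Even complete recording would give only this loose bound, and it holds only if events throughout the period were looked for.

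**The case against.** The strongest case on the other side has four parts.

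- **The two sentences can both hold.** The Harms sentence does not contain the word only. A surgeon could record every event and also report each related one. This stands to the extent that filtering before recording is not proved. It does not settle the matter, because both sentences describe entries by the same person on a case report form, and the Harms section is where a reader looks for the rule.
- **Later ascertainment exists.** The surgeon's second form includes any adverse events, the Harms section sets no time limit, and the Blinding section provides for unmasking after a related serious adverse event, which presupposes that such events come to notice. This stands. A reader might infer that nothing is ascertained after the final capsule, or that events at home would be counted as zero. The article supports neither.
- **This is a condensed article.** Collection windows, follow-up contacts and causality assessment commonly sit in the full protocol, which was ethically approved and is independently monitored. This stands, and the silence about the period at home is not evidence that no procedure exists. The differing scopes and the printed order of form and capsule do not rest on silence.
- **The order may be loose.** Other sections place the last capsule directly after treatment, and nothing says the form cannot be updated. That is fair, but the only section that gives a sequence puts the form first.

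Blinding may also make any relatedness filter even-handed between arms. It would not restore events that were never entered.

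**Conclusion.** The point holds in a limited form. The article gives two scopes for the surgeon's adverse-event record, related events and any events, and they must be reconciled. In the sequence it describes, the first-visit form precedes one third of the dose, and no contact is described as collecting adverse events until the second-extraction form about 4 weeks later, whose look-back period is not stated.

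This rests on reading the First postoperative assessment section as a true sequence, and on the article alone. The full protocol may close the timing gap.

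A reader might also infer that harms are limited to events the surgeon judges related. The Operative variables section contradicts that limit, and no section says who judges relatedness. The effect on event counts cannot be quantified.

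**What to change.** State one rule in both the Harms and the Operative variables sections: all adverse events, whatever the suspected cause, are recorded in both arms from the first capsule to the second visit. Assess relatedness as a separate step, under blinding, after the event has been entered.

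Use contacts that already exist to cover the interval:
- add one adverse-event question to the message sent the day after the first treatment;
- add one to the 4-week preoperative interview, worded to cover the time since the last capsule and asked before the second procedure can produce events of its own.

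If the full protocol already contains such a rule, citing it in the Harms section is enough.

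The cost is one extra item on the case report form and slightly more reporting work. Dose, schedule and visits are unchanged. Because the trial is recruiting, patients already past these contacts will have been recorded under the present wording, and the report should say so.

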## Discussion

We present a study protocol for a randomized controlled trial to test the effectiveness of 120 mg of perioperative propranolol versus placebo to reduce dental trait anxiety, state anxiety during surgery, as well as physiological responses and memory intrusiveness during recall of a crucial fear-related memory. There is a great need for safe and effective interventions since even specialized dental treatments programs, as applied in dental fear clinics, generally fail to alleviate dental anxiety to a clinically significant degree in a significant proportion of the patients [14].

Dental anxiety has been found to exert a great impact on the quality of daily life because of a vicious cycle of declining psychosocial functioning related to anxiety and embarrassment, and severe pain and deteriorating oral health-related problems due to inadequate dental care [20, 67, 68]. Therefore, targeting the reconsolidation of disturbing memories of aversive experiences in which dental anxiety are rooted, with the purpose of helping to transform these into less disturbing memories, may pave the way to a higher treatment success rate in people with high levels of dental anxiety. This would offer support for routinely prescribing of propranolol in patients who are highly fearful of undergoing a dental extraction.

## Trial status

The trial is ongoing and currently recruiting.

## Abbreviations

AMC: Academic Medical Center of the University of Amsterdam
ANCOVA: analysis of covariance
BP: blood pressure
CRF: case report form
FCDS: fear of stimuli compromising the dental setting
GCP: good clinical practice
GMP: good medical practice
HR: heart rate
ICD-10: 10^th^ revision of the International Classification of Diseases and Related Health Problems
IES-R: Impact of Event Scale - Revised
M1: crucial fear-related memory
M2: memory of recent dental extraction procedure
MCQ: Memory Characteristics Questionnaire
MINI: Mini-International Neuropsychiatric Interview
PTSD: post-traumatic stress disorder
QP: qualified person
S-DAI: Short version of the Dental Anxiety Inventory
